#### Secondary hypotheses

The use of a relaxation therapy by breastfeeding mothers of LPI and ETI from one week to eight week postpartum will result in increased breast milk volume, energy carbohydrate and total amount of HMO in breast milk.The use of a relaxation therapy by breastfeeding mothers of LPI and ETI from one week postpartum will have a positive effect on maternal attitudes toward breastfeeding and infant eating behaviour.The composition of microbiome in vaginally delivered infant’s gut and their mother’s milk is associated, and this will be altered by the intervention, with effects on infant appetite, behaviour and temperament.

Secondary outcomes and measures
energy content of breast milk at eight weeks, calculated by milk intake assessed using test weighing methods [21].composition of macronutrients, specifically the lactose and HMO in breast milkcomposition of breast milk microbiota, maternal and infant gut microbiota, measured by the 16S rRNA based amplicon sequencing techniqueinfant appetite at eight week, three month, and six month, assessed using the Baby Eating Behaviour Questionnaire (BEBQ) [22].maternal feeding attitudes at eight week, three month, and six month, measured using the IOWA Infant Feeding Attitudes Scale (IIFAS) [23].infant behaviour, measured by three day infant behaviour diary at eight week.

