#### Test-weighing

For the measurement of milk intake, researchers will lend a digital electronic infant weight scale to mother for 48 h and mother will be asked to weigh her infant right before and right after a feeding, and the duration between the two weight measurements will be recorded to adjust for insensible water loss. Care will be taken to ensure that the infant is weighed with the same clothing before and after the feed. The difference in weight, adjusted for insensible water loss during the feeding period, is the amount of breastmilk the infant consumed during the feeding.

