### Sample management and analysis

#### Breastmilk samples

Milk samples (foremilk) will be collected at first and final home visits. Samples will be collected separately for the analyses of milk composition and microbiota. Some milk will also be stored for measurement of milk hormones, as part of other research ongoing in our research group. The collection will be conducted by either manual expression or using a hand pump (Philips Avent, Netherlands). All samples will be stored at -80°C until analysis.

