#### Analysis of milk energy content

The energy content in breast milk will be estimated from the milk volume measurement using published energy values from the MOM study and the measured energy content in the sample for macronutrients analyses using the MIRIS.

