### Statistical analysis plan

All questionnaires and anthropometric data will be analysed using IBM SPSS (version 24). Intention-to-treat analysis will be performed for comparing primary outcomes (perceived stress and anxiety, infant weight and length gain from baseline to the endpoint) between intervention and control groups at the eight week postpartum using two sample t-test. Paired t-test will be used to compare baseline to post-intervention changes of each primary outcome. The association between the effects of the intervention and the frequency of use will be examined by two-tailed Pearson correlation. Two-sample t-test will be used to compare the changes in milk volume, energy and macronutrients level between intervention and control group. Regression analysis will be used to adjust for confounding factors.

Furthermore, associations between infant temperament/behaviour and the composition of microbiota in mother’s breastmilk, mother and infants’ gut will be examined using univariate ANOVA. Multiple regression analysis and MANOVA will be used to detect differences among significant predictor variables identified by ANOVA.

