## Discussion

One of the strengths of our study is that it has been designed to minimize disruption for the participants since the data collection points have been timed to coincide where possible with routine clinic visits and home visits. According to the health policy in China, the maternity leave is 98 days. During this time, the majority of mothers will practice a traditional postpartum confinement at home and keep routine contact with the community clinic where they are registered. In Beijing, most community clinics will schedule a routine home visit at one week postpartum for all registered mothers. Hence, the baseline assessment of this study is scheduled at one week postpartum when the trained clinic nurses conduct their routine home visit. Thus our baseline assessment and data collection can be conducted during their routine home visit to reduce imposing an extra interruption and additional burden on the mother. Moreover, since there is a routine contact, the nurse can provide the scale and the eight week questionnaires during the contact one week prior to the eight week data collection. Mothers can fill in the questionnaires using their leisure times and return the scale and questionnaires when they take their infant to the clinic for the second month vaccination; the nurse can also conduct the eight week sample collection and infant anthropometry measurement during the time when mothers bring their infants to the clinic for vaccination. These routine contacts with local clinics should help to reduce the potential attrition rate.

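### Milk outcomes are tested as changes, although milk energy is dated at eight weeks, no one-week test-weighing is stated, and baseline-adjusted regression would be more precise for macronutrients

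*Protocol article*

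**What the plan says.** All references are to the protocol article.

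- **Test.** Under Statistical analysis plan, a two-sample t-test will "compare the changes in milk volume, energy and macronutrients level" between the two arms. A later sentence adds regression for confounding factors without naming them.
- **Outcome.** Under Secondary hypotheses, the outcome list gives "energy content of breast milk at eight weeks, calculated by milk intake assessed using test weighing methods". Milk volume has no dated entry of its own, and macronutrient composition carries no time point.
- **Hypothesis.** The same section expects that relaxation therapy "from one week to eight week postpartum will result in increased breast milk volume, energy", among other effects. That wording fits either a level or a change.
- **Milk volume.** Under Test-weighing, "researchers will lend a digital electronic infant weight scale to mother for 48 h"; no visit is named. The one dated loan is in the Discussion: "the nurse can provide the scale and the eight week questionnaires during the contact one week prior to the eight week data collection".
- **Energy.** Under Analysis of milk energy content, "The energy content in breast milk will be estimated from the milk volume measurement", combined with energy values per unit of milk. Total energy therefore depends on when volume is measured.
- **Macronutrients.** Under Breastmilk samples, "Milk samples (foremilk) will be collected at first and final home visits".
- **Allocation.** Randomisation and blinding places it at the one-week home visit, after demographics and feeding history are recorded. The Abstract places it before that visit.
- **Schedule.** Data collection refers to Fig. 3 for what is done at each visit.

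**The concern.** An eight-week level and a change since one week are different analysis variables. The article names the first as the energy outcome and the second as the tested quantity. For volume and volume-based energy, the text does not show that the earlier measurement exists. If it does, its position relative to allocation is unclear: a 48-hour record begun at the one-week visit would continue after a mother had been allocated. Subtracting such a record could remove part of any early effect of the recording.

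For macronutrients the baseline exists and the issue is precision only. An unadjusted change score discards information that a regression on the one-week value would use.

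Increased milk volume and energy open the first secondary hypothesis and are part of the study's overall hypothesis. Leaving level versus change unreconciled also leaves room to choose between them once results are known.

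**Working it through.** **The plan's own figure.** The Sample size section uses N = 16 × SD²/D² with SD = 5.00 and D = 3.13. This gives 16 × 25/9.797 = 40.83, rounded up to 41 per group, so the stated 82 pairs reproduce. That figure concerns perceived stress. The documents give no SD, effect, correlation or power for any milk outcome.

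**Is there a baseline?**

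| Quantity | One week | Eight weeks |
|---|---|---|
| Macronutrient concentration | sample stated | sample stated |
| Milk volume by test-weighing | not stated in the text | scale loan dated in the Discussion |
| Energy based on volume | depends on a one-week volume | stated outcome |

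Change is computable for the first row. For the other two rows it depends on a weighing that the text neither states nor excludes.

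**Precision.** Let rho be the correlation between the one-week and eight-week values. It is assumed and shown over a range. With equal SDs at both times, and the eight-week variance set to 1:

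- variance of change = 2(1 − rho)
- variance after adjustment for the one-week value (ANCOVA) = 1 − rho²
- change ÷ ANCOVA = 2(1 − rho)/[(1 − rho)(1 + rho)] = 2/(1 + rho)

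Power is for 60 per arm (the target of 120 split equally, no dropout), two-sided 5%, normal approximation. The difference is 0.51 SD, an illustrative value at which the unadjusted eight-week comparison has 80% power: (1.96 + 0.84)/√30 = 0.51.

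| rho | Change ÷ eight-week | ANCOVA ÷ eight-week | Change ÷ ANCOVA | Power, change | Power, eight-week | Power, ANCOVA |
|---|---|---|---|---|---|---|
| 0 | 2.0 | 1.00 | 2.00 | 51% | 80% | 80% |
| 0.2 | 1.6 | 0.96 | 1.67 | 60% | 80% | 82% |
| 0.3 | 1.4 | 0.91 | 1.54 | 66% | 80% | 84% |
| 0.5 | 1.0 | 0.75 | 1.33 | 80% | 80% | 90% |
| 0.7 | 0.6 | 0.51 | 1.18 | 95% | 80% | 97.5% |

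Two comparisons must be kept apart. Against ANCOVA, change is less precise at every rho below 1. Against the unadjusted eight-week value, change is less precise when rho is below 0.5, equal at 0.5 and more precise above it.

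**Volume and energy without their own baseline.** If other covariates explain a share R² of the eight-week variance, the adjusted variance is 1 − R². Matching a change score at rho = 0.7 requires 1 − R² = 0.6, so R² = 0.40. Nothing in the documents shows that gestational age, delivery mode, clinic and infant weight would explain that much.

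**The case against.** The strongest reply is that silence in the text is not absence from the trial. The visit schedule is in Fig. 3, the Test-weighing section does not restrict the method to one visit, and the Discussion mentions the scale only while explaining eight-week logistics. The outcome list also tends to name follow-up times only: it dates the behaviour diary at eight weeks, and appetite and feeding attitudes from eight weeks on, yet Table 2 collects all three at one week. An eight-week date for energy therefore does not rule out a one-week measurement. This stands. A reader might infer that the change in volume and energy cannot be computed, and the documents do not support that.

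A reader might also infer that any one-week weighing is a post-randomisation baseline. No section times such a weighing relative to allocation. Parents are contacted before the one-week visit, so an earlier loan is conceivable. The overlap is a possibility, and no size can be put on it.

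A third tempting inference is that testing change loses power in general. It does so against baseline-adjusted regression, but against the unadjusted eight-week comparison the direction reverses above rho 0.5.

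Finally, the article already plans regression adjustment, and its covariates may properly be left to a fuller plan. That is fair, but the article does fix the change-score t-test for these outcomes. What remains is a mismatch between that test and the energy outcome, and an avoidable loss of precision for macronutrients.

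**Conclusion.** The point holds in a limited form. The tested quantity and the dated energy outcome do not match, and the text states no one-week test-weighing. The sections need reconciling, but a missing or post-allocation baseline is not shown.

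For macronutrients, the change-score test is valid, provided the one-week sample is taken before the mother starts the recording. It is less efficient than adjustment for that sample: its variance is 1.67, 1.33 and 1.18 times as large at rho 0.2, 0.5 and 0.7. These ratios rest on equal SDs at the two visits, and rho is assumed throughout.

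The outcomes are secondary and the primary comparisons are unaffected. The point is worth correcting because the correction needs no new data.

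**What to change.** In the Statistical analysis plan section, replace the change-score t-test for milk outcomes as follows.

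- **Macronutrients:** compare eight-week values between arms by regression (ANCOVA), adjusted for the one-week sample and the stratification factors (gestational age band, delivery mode, clinic).
- **Milk volume and energy:** make the eight-week values the analysed outcomes, in line with the secondary outcome list. Adjust for the stratification factors and one-week infant weight, and also for a one-week test-weighing if it was completed before allocation. Do not subtract a weighing made after allocation.
- **Test-weighing:** name the visit or visits at which it is done and, for any one-week record, its timing relative to allocation.

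The cost is a change of wording, with no extra visit, sample or participant. There is one downside: if no pre-allocation weighing exists and rho is high, the adjusted eight-week comparison of volume and energy could be less precise than a change score. The gain from ANCOVA is assured only when the outcome's own baseline is in the model.

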**Discussion:**

Primary outcomes of this study will be the effect of the intervention on maternal psychological state, and infant growth. Other outcomes will include the effect of the intervention on milk production, infant behaviours, and the microbiome composition in breastmilk and maternal and infant’s gut. Results of this study will provide greater understanding about maternal-infant factors which influence the success of breastfeeding, and which may then be useful targets for future interventions.

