### Questionnaires

Questionnaires that will be used in this study are outlined in Table 2. All questionnaires are available in Chinese. The Chinese version of PSS, BAI, BEBQ, and IIFAS have been used among postnatal women in previous studies, which have presented reasonable validity and reliability.

**Table 2 Tab2:** Questionnaires for the BABY study

Questionnaire	Time point for the use of questionnaires			
	First visit 1 week	Final visit 8 week	3 month follow-up	6 month follow-up
Demographic questionnaire	✓			
Perceived stress scale	✓	✓		
Beck Anxiety Inventory	✓	✓		
Baby Eating Behaviour Questionnaire	✓	✓	✓	✓
Iowa Infant Feeding Attitudes Scale	✓	✓	✓	✓
3 day Infant Behaviour Diary	✓	✓		

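### No between-arm test is named for the microbiota, and the one microbiome analysis stated selects predictors by significance and then refits them

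*Protocol article*

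**What the plan says.** **The question.** The Discussion paragraph of the Abstract states: "Other outcomes will include the effect of the intervention on milk production, infant behaviours, and the microbiome composition in breastmilk and maternal and infant’s gut". The third secondary hypothesis (Secondary hypotheses) concerns vaginally delivered infants. It holds that the microbiome of the infant gut and that of the mother's milk are associated, and that "this will be altered by the intervention, with effects on infant appetite, behaviour and temperament".

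**The analysis.** The Statistical analysis plan section names two sets of between-arm tests. Stress, anxiety and infant weight and length gain are compared "between intervention and control groups at the eight week postpartum using two sample t-test". For milk, "Two-sample t-test will be used to compare the changes in milk volume, energy and macronutrients level between intervention and control group".

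For microbiota, the section states a different kind of analysis: "associations between infant temperament/behaviour and the composition of microbiota in mother’s breastmilk, mother and infants’ gut will be examined using univariate ANOVA". The next step is "Multiple regression analysis and MANOVA will be used to detect differences among significant predictor variables identified by ANOVA". Neither sentence mentions the randomised arm.

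**The data.** Under Sample size, the microbiome work is limited to vaginal deliveries, put at about 40% of the sample, with 120 to be recruited. Milk and stool are collected at both the 1-week and the 8-week visit (Breastmilk samples; Stool samples).

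**The concern.** There are two problems.

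1. The stated analysis does not match the stated question. The hypothesis and the outcome list concern an effect of the intervention. The analysis given is an observational association between infant behaviour and microbiota, pooled over arms as far as the text shows. Randomisation does not protect that association from confounding. The Discussion argues that maternal diet should be balanced between the groups, but this helps only a comparison of arms.

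2. The two-step rule takes the predictors that reach significance in ANOVA and puts them into multiple regression or MANOVA. If both steps use the same mothers, the second is conditional on the first having succeeded, so it offers no independent check. Associations that arise by chance would tend to look confirmed, and their estimated size would be inflated by the selection.

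A smaller matter of wording goes with this. Temperament appears in the hypothesis and in the analysis, but no listed instrument measures it. "Questionnaires that will be used in this study are outlined in Table 2", and that table contains no temperament scale. The 3-day diary records sleeping, awake and content, fussy, crying and feeding.

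**Working it through.** **Step 1. The plan's own figure.** The only calculation in the article is for perceived stress (Sample size): N per group = 16 × SD²/D², with SD = 5.00 and D = 3.13. This gives 16 × 25/9.7969 = 40.83, so 41 per group and 82 in total. It reproduces; t-test power at 41 per group is 80.0%. No figure is given for the microbiome analysis.

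**Step 2. Size of the microbiome subset.** 0.40 × 120 = 48 mother-infant pairs, or about 24 per arm if evenly split and none is lost.

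**Step 3. Outcome against analysis.**

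| Outcome | Between-arm test named? |
|---|---|
| Perceived stress, anxiety | Yes, two-sample t-test |
| Infant weight and length gain | Yes, two-sample t-test |
| Milk volume, energy, macronutrients | Yes, two-sample t-test |
| Milk, maternal gut and infant gut microbiota | No; association with temperament/behaviour only |

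**Step 4. What the select-then-refit rule does when nothing is there.** The article does not give the number of candidate predictors, so 10 to 100 is assumed. With m independent candidates tested at 0.05, the chance that at least one passes the screen is 1 − 0.95^m.

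The simulation used 48 mothers, one behaviour outcome and m independent candidates with no true association, with 2,000 runs for each m. Each candidate was screened at p < 0.05 by a one-degree-of-freedom test, standing in for the univariate ANOVA. Those selected were refitted together by multiple regression in the same data.

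| Candidates m | 1 − 0.95^m | Simulated: any pass the screen | Simulated: any significant again on refit |
|---|---|---|---|
| 10 | 40% | 42% | 40% |
| 20 | 64% | 64% | 61% |
| 50 | 92% | 93% | 83% |
| 100 | 99% | 99% | 90% |

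The overall F test of the refitted model was significant in every run in which anything had been selected. The Monte Carlo standard error is about one percentage point, for example √(0.40 × 0.60/2000) = 0.011. The refit therefore adds almost no protection at small m and little at large m.

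**Step 5. What a between-arm comparison could detect.** Putting N = 24 into the plan's own formula gives D/SD = √(16/24) = 0.82; the t-test calculation gives 0.83. For a standardised difference equal to the one assumed for perceived stress (3.13/5.00 = 0.626), power at 24 per arm is about 56%. Using that effect size for a microbiome measure is an assumption, since the article gives none.

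**The case against.** The strongest reply is that a condensed article has been read too literally. The Abstract names the effect on the microbiome as an outcome, and the Discussion's remark about balanced diet makes sense only if arms are to be compared. The comparison is evidently intended. The choice of test, diversity measure and error control is commonly left to a fuller plan. The same section is also silent on between-arm tests for appetite and feeding attitudes, which suggests condensation.

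Much of this stands. A reader might infer that the trial cannot answer its microbiome question. The documents do not support that: randomisation is stratified by delivery mode, and samples are planned at both visits, so a valid comparison is available. What remains is narrower. For microbiota the section is not merely brief. It specifies an analysis, and that analysis does not address the randomised question.

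The second reply is that the text speaks of composition and predictor variables, not of taxa, and does not say that both steps use the same data. This is also fair. The predictors could be a few summary measures, in which case the low end of the range applies. Use of the same data is inferred because no other sample is mentioned. Selection by ANOVA significance, however, is stated outright.

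A reader might also infer that antibiotic use is ignored. That is not shown. The assessment is restricted to vaginal deliveries partly for that reason, antibiotic use is recorded, and the section has a general sentence on adjusting for confounders.

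**Conclusion.** The point holds for the document as written. The Statistical analysis plan section names no between-arm test for microbiota, although the intervention's effect on them is an outcome and part of a secondary hypothesis. The one microbiome analysis it does state uses a selection rule that cannot confirm its own findings.

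Under a global null, at least one predictor survives the refit in about 40% to 90% of runs for 10 to 100 candidates. These figures assume 48 mothers, one behaviour outcome, independent candidates and both steps in the same data. Correlation among candidates would change them; more behaviours or sample types would add further tests.

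It would go too far to conclude that most reported associations would be false. That share depends on how many true associations exist, and a global-null simulation does not address it.

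This is a secondary outcome, but the gut microbiome is in the title and the subset is given as a reason for a larger sample. The text should be changed.

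**What to change.** Revise the microbiome paragraph of the Statistical analysis plan section as follows.

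- **Main analysis.** For each sample type (milk, maternal gut, infant gut), compare the randomised arms within the vaginal-delivery stratum on 8-week composition and diversity. Take the 1-week samples into account and respect the remaining randomisation strata, centre and gestational age. One workable choice among several is a permutation MANOVA on a between-sample distance, permuting within centre-by-gestational-age cells and adjusting for a summary of 1-week composition. Diversity could be analysed by ANCOVA on its 1-week value and the strata.
- **Individual features.** Test them between arms with the false discovery rate controlled.
- **Milk–infant gut link.** State a test of whether this association differs by arm, for example by comparing the within-pair milk–infant gut distance between arms.
- **Behaviour associations.** Label them exploratory, put all candidate features in one false-discovery-rate family, and drop the significance pre-screen.
- **Temperament.** Align the term in the hypothesis and the analysis with the diary behaviours actually measured.

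The cost is wording and modest analysis work on samples that are already planned; no new data are needed. Fewer features will be nominally significant. With about 24 per arm, only differences of about 0.83 SD are detectable at 80% power, and the report should say so.
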